A patient who is randomly allocated to the craniotomy group, but finally receives a decompressive craniectomy as a lifesaving action during the initial surgery, will be rejected from this randomized controlled trial. This potential selection bias is beyond the control of the investigators, and according to the current guidelines, no specific surgical options are provided for the enrolled participants. Nevertheless, patients’ detailed data will be recorded, providing the observational cohort information necessary to further analyze the possible factors and potential bias.

Due to the nature of the intervention, and the risk that DC surgical procedure will result in skull defect, patients and treating doctors cannot be blinded to allocation. However, the evaluators involved in this study and the investigators responsible for the outcomes’ analysis are blinded to the groups.

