### Aims and outcomes

The trial aims to evaluate craniotomy and DC on AEDH patients in terms of efficacy, economic benefits, and complications. The primary endpoint is the Glasgow Outcome Score-Extended (GOSE) at 6 months post-injury, the most commonly used prognostic evaluation scale in TBI, which allows the assessment of the long-term functional outcomes, including overall mortality and morbidity rates [8, 9].

Additionally, the following secondary endpoints are intended to be investigated as supplementary functional and cognitive measures:
The incidence of postoperative cerebral infarction within 6 months post-injury, to be primarily diagnosed by independent radiologists by CT or MRI examinationThe incidence of additional craniocerebral surgery, as a result of clinical deterioration after initial surgical treatment for AEDH, within 6 months post-injuryThe incidence of serious adverse events (SAE) within 6 months post-injury, and SAE is defined as an untoward occurrence that:
Results in deathIs life-threateningRequires hospitalization or prolongation of existing hospitalizationResults in persistent or significant disability or incapacityIs otherwise considered medically significant by the investigatorThe length of patient’s stay in ICU and hospital after initial surgery within 6 months post-injuryDetailed economic evaluation, defined as the total medical expenses related to the treatment for AEDH, including the costs of operations, hospitalization, and rehabilitation within 6 months post-injuryQuality of life at 6 months post-injury with the score of 5-level EuroQol Five Dimensions Questionnaire (EQ-5D-5L). The EQ-5D is a generic instrument to describe and evaluate the health condition on the basis of five dimensions: mobility, self-care, usual activities, pain/discomfort, and anxiety/depressionMMSE (Mini-Mental State Examination) scores at 6 months post-injury

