### Data collection

Once patients are enrolled in the study, data related to demographic and clinical information, including hospital admission, treatment process, and follow-up, will be collected by the local investigators and recorded on the case report form (CRF). Detailed data consisting of neurological condition, timing of injury (also the ER, initial CT, and surgical operation), radiographic abnormalities, operation data, and postoperative care management (including ICP management and pharmacological data) will also be recorded. Postoperative CT scan will be performed routinely on the 1st, 3rd, and 7th day post-initial surgery. Cerebral infarction will be initially detected by postoperative CT image depicting a low-dense area. The blood supply of involved lobes will be further detected by transcranial Doppler sonography (TCD) and/or MR. Follow-up visits in the outpatient department are scheduled at 1, 3, and 6 months after injury; data will be collected and recorded. The information recorded on CRFs will be entered into an electronic data collection (EDC) database by a designated person within each participating center. A subject must be withdrawn from the trial if one of the following applies:
Each patient or his/her legally authorized representative has the right to require withdrawal from the study cohort for any reasons after enrollment.The investigator will withdraw a patient who is randomly allocated to a craniotomy and that eventually requires a DC as lifesaving action during the initial surgery.In addition, the investigator could withdraw the patients from their allocated treatment group if a clinical reason for not performing the surgical intervention is identified after randomization.Lost to follow-up.

The primary reason for all discontinuations and withdrawals will be documented.

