So far, there is no reliable data able to clarify the potential selection bias caused by the number of patients who, after initial allocation to a craniotomy, eventually require a DC. This study aims to be a pragmatic trial to improve and specify the surgical options for AEDH. Data of patients who, after initially undergoing craniotomy, eventually require a DC will be recorded, as the incidence of additional craniocerebral surgery after the initial surgical treatment (secondary endpoint). All these information will help in evaluating the potential selection bias.

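### The additional-surgery endpoint, offered as information on selection bias from craniotomy patients who need a DC, cannot register conversions during the initial operation and so omits those failures of the craniotomy strategy

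*Protocol article*

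**What the plan says.** The protocol article deals with craniotomy-allocated patients who end up with a DC in four places.

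- **Sample size calculation, randomization, and blinding.** A patient allocated to craniotomy who "finally receives a decompressive craniectomy as a lifesaving action during the initial surgery, will be rejected from this randomized controlled trial". The next sentence calls this a potential selection bias. The section adds that these patients' "detailed data will be recorded, providing the observational cohort information necessary to further analyze the possible factors and potential bias".
- **Data collection.** The withdrawal list includes a patient "randomly allocated to a craniotomy and that eventually requires a DC as lifesaving action during the initial surgery". The main reason for every withdrawal is to be documented.
- **Aims and outcomes.** One secondary endpoint is the "incidence of additional craniocerebral surgery, as a result of clinical deterioration after initial surgical treatment for AEDH", within 6 months of injury.
- **Data analysis, last paragraph.** It notes that no reliable data exist to clarify "the potential selection bias caused by the number of patients who, after initial allocation to a craniotomy, eventually require a DC". It then says that data of patients who first undergo craniotomy and "eventually require a DC will be recorded, as the incidence of additional craniocerebral surgery after the initial surgical treatment (secondary endpoint"), and closes: "All these information will help in evaluating the potential selection bias".

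**The concern.** The randomisation section locates the selection bias in patients converted to DC during the initial operation. When Data analysis returns to the bias, the only record it names is an endpoint that starts after that operation. The people who create the bias lie outside the measure offered to evaluate it.

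Two things are at stake. First, a low rate of additional surgery could be cited as reassurance that selection bias is small, although the rate says nothing about conversions. Second, readers will compare the rate between arms as a guide to how often each strategy proves insufficient. In the craniotomy arm, the patients in whom it proved insufficient at once are missing from both numerator and denominator. Whether a DC counts then depends on whether it is done before or after the end of the first operation, and the operating surgeon is unblinded.

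**Working it through.** **1. The definitions side by side**

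| Craniotomy-allocated patient | Status in the trial | Event under Aims and outcomes? |
|---|---|---|
| DC during the initial operation | Rejected or withdrawn | No, and not in the denominator |
| Craniotomy completed, later surgery for deterioration | Retained | Yes |
| Craniotomy completed, no later surgery | Retained | No |

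The wording hides the difference between the first two rows. Data collection uses the phrase for the intraoperative case ("eventually requires a DC as lifesaving action during the initial surgery"). Data analysis uses almost the same phrase for patients whose DC is recorded as surgery after the initial treatment. One expression covers two groups that do not overlap.

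**2. Inputs**

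- Craniotomy-allocated patients: 120 in total at 1:1, so 120 / 2 = 60 (Sample size calculation, randomization, and blinding).
- c, the share converted during the initial operation: not given; assumed.
- r, the rate of later additional surgery for deterioration among those who remain: not given; assumed. The endpoint counts any such craniocerebral surgery, not only DC.

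The document states no rate for either quantity, so there is no figure of its own to reproduce.

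**3. Direction**

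- Rate shown once converters are removed: r.
- Share of all allocated patients with conversion or later surgery: c + (1 − c)r.
- Difference: c + (1 − c)r − r = c(1 − r).

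The difference is positive for any c > 0 with r < 1 and zero when c = 0, so the direction is fixed. The rate shown does not contain c, so nothing about the number of conversions can be learned from it.

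**4. Illustration with assumed rates**

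| r | c | Converted, of 60 | Endpoint shows | Conversion or later surgery, of all 60 | Share not shown, c / [c + (1 − c)r] |
|---|---|---|---|---|---|
| 10% | 0% | 0 | 10% | 10.0% | 0% |
| 10% | 5% | 3 | 10% | 0.05 + 0.95 × 0.10 = 14.5% | 34% |
| 10% | 10% | 6 | 10% | 0.10 + 0.90 × 0.10 = 19.0% | 53% |
| 10% | 20% | 12 | 10% | 0.20 + 0.80 × 0.10 = 28.0% | 71% |
| 5% | 10% | 6 | 5% | 0.10 + 0.90 × 0.05 = 14.5% | 69% |
| 20% | 10% | 6 | 20% | 0.10 + 0.90 × 0.20 = 28.0% | 36% |

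**5. Would restoring converters to the denominator be enough?**

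Suppose they are kept, the endpoint is unchanged, and none of them has later surgery. The rate is then (1 − c)r. With r = 10% this is 9.5%, 9.0% and 8.0% for c = 5%, 10% and 20%. The conversions are still invisible, so the conversion count has to be reported as well.

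**The case against.** The best case for the protocol has five parts.

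- **The trial does keep the information.** The randomisation section retains converters' data expressly to study potential bias, and Data collection documents withdrawal reasons. This stands. A reader might infer that the trial cannot quantify conversion. The documents do not support that: the limit belongs to the endpoint, and the number of converters is recoverable.
- **The endpoint is a correctly named re-operation rate.** In a converter the flap was never replaced, so leaving converters out is right if the question is re-operation after a completed craniotomy. This stands too. The understatement arises only when the rate is read as a comparison of the strategies as allocated, which is the comparison that randomisation supports.
- **The text claims little.** It says the information will help, not that this endpoint is the sole measure, and its description of the bias is broad enough to include delayed DC. So the paragraph is incomplete rather than false. It still points to no source for the intraoperative group, which the randomisation section ties to the bias.
- **The real problem is the post-randomisation exclusion.** In large part, yes. But step 5 shows that changing the analysis population alone would leave conversions uncounted.
- **Adding conversion to the event definition tilts the comparison.** Counting receipt of the comparator operation as an event in one arm has no counterpart in the other. This stands, and it argues against redefining the endpoint.

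**Conclusion.** The point holds in a limited form. As defined, the additional-surgery endpoint carries no information on the number of intraoperative conversions, so it cannot by itself support the evaluation of selection bias for which Data analysis cites it. Read as a comparison of allocated strategies, it understates failure of craniotomy by c(1 − r) whenever at least one conversion occurs. That reading treats the need for a DC during the initial operation as a failure of the allocated strategy.

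The size is unknown. The illustrated gaps (10% shown against 14.5% to 28.0%) rest wholly on assumed rates, and with no conversions the gap is zero. A reader might infer that some definite fraction of the DCs needed goes uncounted. The documents do not support that, because they give no rates and the endpoint is not restricted to DC.

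**What to change.** - **Aims and outcomes.** Keep the endpoint as defined, but state that it is analysed by allocated arm with all randomised patients in the denominator.
- **Reporting.** Beside it, as a separate component, give the number and proportion of craniotomy-allocated patients converted to DC during the initial operation. Add a supplementary rate of conversion or later unplanned surgery, labelled as one-sided by construction.
- **Data analysis, last paragraph.** Base the evaluation of selection bias on the conversion count and the observational data that the randomisation section already promises.
- **Wording.** Reconcile Data collection and Data analysis so that conversion during the initial operation and DC at a later operation have different names. The rejection and withdrawal statements must be made consistent with the all-randomised denominator.

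The cost is small. Surgery notes are scheduled in Table 1, and converters' data and withdrawal reasons are already to be recorded. The additions are some reporting and a statement that converters' later operations are captured to 6 months, since the article does not say how long their data are collected. The supplementary composite has no counterpart event in the DC arm, so it should be descriptive and always shown with its components. No surgical decision changes.

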### Ethics and dissemination

The study protocol has been approved by the ethics committee and institutional review board of Renji Hospital, School of Medicine, Shanghai Jiao Tong University (KY2020-038), representing the center that supports this research. Other participating centers will be separately evaluated in their participation from each ethics committee or institutional review board. During the research process, the study investigators will strictly follow the Declaration of Helsinki and Human Biomedical Research Ethical Issues. Any protocol amendments will be first submitted to the review board for approval. The management process and medical treatment of the enrolled participants will not be affected by their recruitment into the PREDICT study. In case of death or occurrence of serious adverse events, a detailed report will be sent to the ethics committee and institutional review board of the leading research center.

All enrolled participants will be asked to provide a signed informed consent to produce documentary evidence on the information received on the clinical trial, the study interventions, participants’ rights, and the voluntary nature of their participation. Predictably, most eligible participants will be incapacitated to give consent for trial entry themselves, due to the brain injury. If the next of kin are available, they will be asked to give proxy consent for the patient’s admission. A brief discussion explaining the patient’s participation in the study will take place face to face or by telephone. If the next of kin are unavailable or cannot be reached before the operation, the principal investigator will take responsibility for including the patient into the trial, provided that the following conditions are met:
The patient is eligible for trial entry.The patient is in a life-threatening situation and an urgent operation is required without delay.Operation is not detachable from decompressive craniectomy or craniotomy during the treatment of a patient undergoing evacuation of an acute epidural hematoma.Both decompressive craniectomy and craniotomy are well established in the treatment center and routinely performed by the investigator.Investigator documents in the declaration form are approved by the ethics committee and institutional review board of the treatment center.

Best efforts will be made to contact the next of kin during the treatment and seek their approval to the patient’s inclusion within the trial. Views of withdrawal to enter or continue the trial from next of kin will be respected, and no further data will be collected from the patient.

If participants regain their decisional capacity during the procedure, they will be given information about the trial and their consent will be sought to continue in the trial. Meanwhile, participants or next of kin are also informed that they could withdraw consent and quit at any moment during trial, without affecting their treatment process, only by informing the investigator on their willingness to keep their collected data for future analysis or delete them.

No patients or the public were directly involved in the design or conduct of the study. The patients and their caregivers will be informed about the whole duration of the study (4 years), and any development may occur during the process. The trial results will be disseminated through academic conferences and published in peer-reviewed journals. In case of publication, the investigators will immediately inform the patients and their caregivers by telephone or e-mail.

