### Sample size calculation, randomization, and blinding

Our data and results from a previous retrospective study are showing that almost all the patients who received a synchronous DC (93%) had a GOSE of 6.63 ± 1.27, with a favorable outcome (defined by the GOSE categories: lower moderate disability, upper moderate disability, lower good recovery, and upper good recovery). Patients who received craniotomy had a GOSE of 5.78 ± 1.58, with a favorable outcome in 72% of the patients [6]. We calculated the sample required in this clinical trial with a significance level of 5% (two-sided) and a power of 80% to demonstrate the difference in the rate of favorable outcome, with an assumption that 10% of the patients would be lost during follow-up. Ultimately, considering the quality of the study, the sample size is enlarged to 120.

All participating centers must have a neurosurgical on-call team and an emergency department responsible for the admission of head-injured patients to identify eligible patients. After recording the patient’s clinical information, including Glasgow Coma Scale (GCS), pupillary reactivity, and CT findings, an electronic data collection (EDC) database will generate the subject identification number that will be allocated to the eligible patients. A secure central web-based randomization management information system will be used for the randomization of eligible patients. The system will provide an immediate allocation along with the patient randomization record number for the trial, and individual randomization record numbers can be checked at any time. Blocked randomization will be used, with a block size of 4 and an allocation ratio of 1:1. The 24-h central web-based randomization management information system will be backed by one delegated person (available 24 h per day) who will assure the cover-up of the record allocation. The delegated person responsible for randomization will not be involved in the treatment procedure. A confirmatory email will be sent to the investigator of each center involved to verify the allocation.

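### Stopping all data collection when next of kin withdraw gives up the 6-month GOSE, and that loss can depend on arm and outcome

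*Protocol article*

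**What the plan says.** All of the consent text is in the protocol article under Ethics and dissemination. It expects most eligible patients to be unable to consent for themselves. Next of kin give proxy consent if available. If they cannot be reached before the operation, "the principal investigator will take responsibility for including the patient into the trial", subject to listed conditions. Relatives are then sought during treatment, and a decision not to enter or "continue the trial from next of kin will be respected, and no further data will be collected from the patient".

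A second consent step follows for some patients: "If participants regain their decisional capacity during the procedure, they will be given information about the trial and their consent will be sought to continue". Participants or next of kin may quit at any time without effect on treatment, informing the investigator "on their willingness to keep their collected data for future analysis or delete them".

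Four other parts of the article bear on this:

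- The blinding text states that patients and treating doctors cannot be blinded.
- Treatment interventions states that the arms differ only in whether the bone flap is removed or replaced, and that later care is unaffected by recruitment.
- Data collection treats withdrawal as leaving the study cohort and requires the primary reason to be documented.
- Aims and outcomes makes GOSE at 6 months the primary endpoint.

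**The concern.** The randomised treatment is one operation. Once it is done, continuing in the trial means essentially allowing data to be collected. A rule that ends all collection when relatives refuse therefore protects nobody from a trial procedure, yet gives up the primary endpoint for that patient.

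Two features make the loss potentially selective. First, the renewed request for consent goes to patients who regain capacity, a group formed after randomisation and closely related to GOSE. Patients who die or remain incapacitated do not receive it, and for them the decision lies with relatives. Second, whoever decides can know the arm, because decompressive craniectomy (DC) leaves a skull defect and cranioplasty is normally recommended afterwards. Missing GOSE could thus be related to both arm and outcome. Outcomes never collected, or records deleted on request, cannot be recovered by any later analysis.

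The article does see the value of continued recording elsewhere. Craniotomy-arm patients rejected from the trial because they received DC at the initial surgery still have detailed data recorded. No comparable provision is described for withdrawal of consent.

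**Working it through.** **Inputs from the article** (Sample size calculation, randomization, and blinding)

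- DC: "almost all the patients who received a synchronous DC (93%) had a GOSE of 6.63 ± 1.27"; the 93% is used here as the favourable rate.
- Craniotomy: "Patients who received craniotomy had a GOSE of 5.78 ± 1.58, with a favorable outcome in 72% of the patients".
- Total 120, allocated 1:1, so 60 per arm. Allowance for loss 10%, not split by arm, outcome or reason.
- Refusal rates: none given. Every refusal rate below is an assumption.

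**1. The plan's own figure.** The calculation uses "a significance level of 5% (two-sided) and a power of 80" per cent. With the pooled-variance formula for two proportions, mean rate 0.825:

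n = [1.96√(2×0.825×0.175) + 0.842√(0.93×0.07 + 0.72×0.28)]² / 0.21² ≈ 50.2, so 51 per arm and 102 in total. Then 102/0.90 = 113.3, so 114.

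The article does not state its N before enlargement, but 114 fits an enlargement to 120. If 10% are lost in each arm regardless of outcome, 54 per arm remain, power is about 83% and there is no bias. The sample size is not the issue.

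**2. Expected outcomes at planned rates.** Favourable: 60×0.93 ≈ 56 in DC and 60×0.72 ≈ 43 in craniotomy. Unfavourable: 60×0.07 + 60×0.28 = 4.2 + 16.8 = 21. A few selective losses among 21 matter.

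**3. Effect on the favourable/unfavourable odds ratio (DC v craniotomy).** If a fraction r of favourable patients leaves an arm, its odds are multiplied by 1−r. If a fraction u of unfavourable patients leaves, its odds are divided by 1−u. The overall loss assumes 72% favourable in both arms, that is, no true effect.

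| Assumed loss | OR multiplied by | Overall loss |
|---|---|---|
| Favourable: 15% DC, 5% craniotomy | 0.85/0.95 = 0.895 | (10.8% + 3.6%)/2 = 7.2% |
| Favourable: 20% DC, 5% craniotomy | 0.80/0.95 = 0.842 | (14.4% + 3.6%)/2 = 9.0% |
| Unfavourable: 0% DC, 20% craniotomy | 1−0.20 = 0.80 | (0% + 5.6%)/2 = 2.8% |

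All three fit within the 10% allowance. The last needs only 0.20×16.8 ≈ 3.4 patients.

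**4. Against sampling error.** With 60 per arm and 72% favourable in both, SE(log OR) = √[2(1/43.2 + 1/16.8)] ≈ 0.41. The three factors shift log OR by 0.11, 0.17 and 0.22, or about 0.3, 0.4 and 0.55 SE. Two-sided type I error rises from 5% to roughly 6%, 7% and 8.5%. At planned rates the OR is (0.93/0.07)/(0.72/0.28) ≈ 5.2; multiplied by 0.842 it is about 4.4.

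**5. Range on the risk-difference scale, no true effect, 72% in both arms.**

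- Milder: unfavourable loss 20% in DC and 0% in craniotomy, favourable loss 10% in both. DC 0.648/(0.648+0.224) = 74.3%; craniotomy 0.648/(0.648+0.28) = 69.8%; spurious difference 4.5 points. Other mild patterns reached 7.3 points.
- Extreme: 10% lost per arm, all unfavourable in DC and all favourable in craniotomy. DC 0.72/0.90 = 80.0%; craniotomy 0.62/0.90 = 68.9%; spurious difference 11.1 points, with about a 26% chance of significance at 54 per arm. The reverse pattern gives −11.1.

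**6. What analysis could still do.** If 93% v 72% were observed with 10% missing per arm, the worst-case bounds on the true difference are 0.837−0.748 = 8.9 points and 0.937−0.648 = 28.9 points. Sensitivity analysis can bound the loss but cannot undo it.

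The primary analysis is ordinal logistic regression over the full GOSE. None of these figures is for its common odds ratio.

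**The case against.** The best defence is that respecting a refusal made for an incapacitated patient is an ethical choice and not a statistical error, and that a condensed article commonly leaves detailed consent options to the full protocol, consent form and CRF. This stands in part. If those documents already offer graded withdrawal, the sponsor need only say so. But the sentence on next of kin is not silence: it states a rule, and the rule as worded leaves no room for an intermediate option.

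Several stronger readings are tempting, and the text does not support them.

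- A reader might call withdrawal all-or-nothing. It is not, because those who quit may choose to keep the data already collected. What is absent is an option for outcome data still to come.
- A reader might infer that any refusal ends data collection. That sentence is written only for next of kin. For participants it could be inferred from their right to quit, but the article does not say it.
- A reader might take re-consent to fall after the operation by rule. The wording places it during the procedure. After surgery is the likely meaning for herniated patients undergoing emergency evacuation, but it is an inference.
- A reader might think that only recovered patients can leave. Next of kin may also withdraw at any time; only the renewed request is specific to those who regain capacity.
- A reader might fear that deleted deaths vanish altogether. Deaths and serious adverse events are also reported to the lead ethics committee, so the threat is to the analysis dataset.

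It is also fair that the odds-ratio factors concern a secondary analysis, rest on assumed rates and opposing mechanisms, and are modest next to the sampling error. Nothing shows which mechanism, if any, would operate.

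**Conclusion.** The concern holds in a limited form. The stated rule forgoes the 6-month GOSE when next of kin refuse or withdraw, although the randomised treatment will usually be complete, and it allows collected data to be deleted. The position for participants who regain capacity and quit is left unclear. Because the arm is known and the renewed request goes to a group related to outcome, the loss can depend on arm and outcome. A reader might infer that it does; the documents give no refusal rates and cannot show that.

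Under the assumed rates, the secondary favourable/unfavourable odds ratio would be multiplied by about 0.80 to 0.89, with type I error of roughly 6% to 8.5%. A bias of 11.1 points requires an extreme pattern. The effect on the primary common odds ratio was not computed. This does not invalidate the design, but the loss is avoidable, cannot be repaired later and is cheap to reduce.

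**What to change.** Replace the blanket rule for next of kin with graded withdrawal, apply it equally to participants who regain capacity, and record the chosen level on the CRF:

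- (a) stop visits but allow a telephone GOSE at 6 months;
- (b) stop all contact but allow vital status and outcome to be taken from routine records;
- (c) no further data.

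Offer (a) first when consent is sought again. By default, keep data collected up to withdrawal, including deaths and serious adverse events, in the allocated arm unless deletion is expressly requested, subject to ethics approval. Report withdrawals and deletions by level and arm.

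The cost is revised wording in the protocol and consent form, one CRF item, an ethics amendment and a slightly longer consent conversation. The right to withdraw fully is unchanged, and the sample size need not be altered on this account.
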